#### Maternal vaginal microbiota

Two vaginal samples will be collected to study changes in vaginal microbiota between baseline and 8 weeks after the start of the intervention. Participants will collect the samples by rotating swabs 3–4 cm deep into the vagina. Samples will be collected by the validated self-collection method using dry swabs [65]. The samples will be immediately stored at − 20 °C, collected by investigators at t1 or t4 and then stored at − 80 °C at the Radboud University. Microbial composition will be determined using polymerase chain reaction (PCR) sequencing methods at affiliated universities experienced in this type of analysis; the location for these analyses has yet to be determined.

#### Maternal intestinal microbiota

Participants will collect fecal samples twice using collection methods applied in our previous studies [36, 38], in order to study changes in maternal intestinal microbiota between baseline and 8 weeks after the start of the intervention. For storage procedures, see “Maternal vaginal microbiota”.

#### Infant intestinal microbiota

Parents will collect two infant fecal samples at home on weeks 1 and 4 using similar collection methods to those applied in our previous studies [36, 38], to measure the relative abundance of infant intestinal bacteria. Samples will be immediately stored by the participants at − 20 °C, collected by investigators at t3 and taken back to the University for storage at − 80 °C. The microbial composition of the stool samples will be analyzed using PCR sequencing methods.

### Possible confounding variables

Maternal sleep and stressful events will be measured throughout the study period, as both factors may influence the intestinal microbiota in mothers and infants, as well as maternal mood [55, 66, 67].

#### Pittsburgh Sleep Quality Index

Sleep quality is measured using the Pittsburgh Sleep Quality Index (PSQI), a self-rated questionnaire that assesses sleep quality and disturbances during the previous months [68]. The PSQI has demonstrated good psychometric properties, including good internal consistency and validity in pregnant women [69]. We will use the Dutch translation of the PSQI, which has been commonly used in Dutch populations [36, 70]. The sum of scores ranges between 0 and 21 and scores ≤ 5 and > 5 indicates “poor sleepers” and “good sleepers”, respectively [68].

#### Stressful events questionnaire

Other systematic reviews have noted the stressful events that can predict prenatal anxiety and depression [71, 72]. Based on these studies, we constructed a new stressful events questionnaire that assesses whether or not participants experienced one or more stressful events during the past 12 months. The questionnaire includes 8 items (i.e. death of a close relative/family member, financial problems, divorce etc.) on a dichotomous scale (yes/no). More reported stressful events indicates higher incidence of stressful events.

### Adherence assessment

To facilitate adherence to the study protocol and increase the validity of data, throughout the study the CI will inquire about participants’ experiences during the trial, including potential problems with the probiotic/placebo product intake, questionnaires and collection of vaginal and stool samples. In the case of problems, the CI will discuss solutions with the participants to improve adherence. After 8 weeks of probiotic intake (t1) the CI will call to inform the participant about the number of sachets consumed during the intervention period and will record the number on the CRF. At t4, the CI will measure compliance during a home visit by counting the sachets that are left from the previous weeks and notes the data on the CRF. Electronic questionnaire data collected from participants will be downloaded into a designated secure Radboud University study computer to check for missing data. In the case of missing questionnaire data, the CI will send an e-mail reminder to the participant with the request to fill in the questionnaire as soon as possible. The CI will record non-adherence and non-retention (i.e. consent withdrawn and loss to follow up) on the CRFs, and the reasons for non-adherence and non-retention if the participants are willing to reveal these.

### Strategies to improve adherence to the intervention protocol

During the first home visit when the participants receive the probiotic/placebo product and sampling kits, the CI will provide face-to-face adherence reminder sessions. Similar adherence reminder sessions will be held by phone at t1 and t3, and face-to-face at t4. This will include:Explanation about the importance of adhering to study guidelines on the daily intake of the study product, electronic questionnaires and collection of vaginal and microbial sampling.Instructions about taking the probiotic/placebo product, including timing, preparation, storage, and what to do in the event of missing a dose.Reinforcement that the sachets contain either probiotics or placebo.Instructions about the purpose and use of vaginal swabs and microbial collection tubes, and temporary storage of vaginal and microbial specimens after collection. Instructions on paper will be provided at t0 (see Additional file 3D-E).Notification of the importance of contacting the CI if experiencing any problems related to intake of the probiotic/placebo product (e.g. symptoms, lost sachets), electronic questionnaires or the collection of vaginal and/or microbial samples.Reinforcement that, if there are any questions related to the study or problems occur during the intervention period, the CI (or in case of absence, another research member) can be contacted by phone or e-mail.

Within 2 days after the first home visit, the CI will contact the participant to ask whether there were any problems with the probiotic/placebo product or questionnaires, and to inform them about the time/date of collecting vaginal and stool samples. In case there are problems, simple strategies for enhancing adherence to study protocol will be discussed. The participant will also have the opportunity to ask the CI any remaining questions.

Participants will receive an electronic reminder at t1 to fill in questionnaires and to collect vaginal and microbial samples, again including the instructions about the use of vaginal swabs and microbial tubes and storage of specimens after collection. The CI will contact the participant 2 days after the first reminder, to request the time/date of collection of microbial and vaginal samples. In the case of problems, the CI will discuss with the participant simple strategies to enhance collection and/or filling in of questionnaires.

### Plans to promote participant retention and complete follow up

Several methods will be applied to promote participant retention, including financial reimbursement (€65) and by limiting participant burden (i.e. by conducting home visits and by allowing participants who decline specific assessments for one outcome to continue with assessments for other follow-up outcomes).

### Training and certificates of investigators

To promote consistency in data collection and enhance data quality, the CI and Research Physician will be trained in medical scientific research, legislation and regulation to carry out clinical research. Passing the national examination of the basic course for clinical investigators (BROK®) will certify their competencies as clinical investigators. Additionally, the CI will be trained in standardized collection of hair samples at Radboud University, will receive training at the Amsterdam University Medical Centers on entering information on to the CRFs and responding to data discrepancies and training in qualitative research at the Vrije Universiteit Amsterdam.

### Data management

Data recorded on paper forms (e.g. Baby’s Cry Diary) will be entered into the computer by data entry personnel at the Sponsor site, using double data entry. Researchers who score the duration of crying diaries will be blinded to the treatment arms. Data integrity on Microsoft Excel spreadsheet charts will be enforced through referential data rules, range and consistency checks against data already present in the database. Independent source document verification of a random subset of CRFs will be performed to detect data entry errors. Data recorded on paper (e.g. CRFs) will be securely stored in numerical order at the Radboud University. Electronic data (i.e. online questionnaires and electronically entered data from CRFs) will be stored on the university server using password-protected access systems only known to the trial committee researchers and research assistants. Data backup will be performed daily. Hair and biological samples will be retained at the Sponsor site until the study is completed and then sent to collaborative universities for analysis through secure mail. In concordance with Good Clinical Practice (GCP) guidelines, electronic data and informed consent forms will be retained for at least 15 years after completion of the pilot study.

### Statistical analysis

#### Primary quantitative outcomes

The primary outcomes, (A) recruitment, (B) retention rate, (C) compliance and (D) (1–5) participants’ impressions and experiences, will be descriptively analyzed and visualized in tables or graphs: number and percentages will be calculated for categorical variables and mean (or median) and SD (or IQR) will be calculated for continuous variables. For outcome (D) (1–3), participants’ impressions and experiences, the main themes and categories of participants’ responses will be identified (see “Primary qualitative outcomes” for description of conventional content analysis and the framework approach) and quantified [73, 74]. The prevalence of coded themes will be calculated as a percentage of the total number of identified coded themes. Demographic data on subjects (general health, socio-economic factors, etc.) will be tabulated.

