### Objectives

The main aim of this pilot trial is to evaluate the feasibility and acceptability of conducting a definitive RCT among pregnant women with symptoms of depression or anxiety. Feasibility is evaluated in terms of (A) recruitment and (B) retention, and acceptability is evaluated in terms of (C) compliance and (D) participants’ experiences of participating in the study. The primary objectives are to quantitatively and qualitatively assess (A) the proportion of pregnant women with depressive and/or anxiety symptoms accepting the invitation to participate in the pilot trial and the reasons why (quantitative and qualitative), (B) the proportion of women who complete the study (quantitative), (C) adherence rates to the intervention schedule (i.e. probiotic/placebo intake, questionnaires and biological sample collection) (quantitative) and (D) participants’ impressions and experiences during the pilot trial (quantitative). The secondary aim is to exploratorily compare the potential effect of probiotics, compared to placebo, on depressive and/or anxiety symptoms, maternal stress (i.e. reported and hair cortisol), maternal vaginal and intestinal microbiota, and by possibly affecting maternal mood and microbiota, maternal bonding to offspring, infant microbiota and infant crying. The purpose of collecting these secondary outcomes will be to ensure that the potential effects of probiotics on maternal mood, and the mechanisms underlying these potential effects, can be assessed appropriately in a future definitive RCT.

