### Randomization, blinding and treatment allocation

The 40 women will be randomly allocated to either the probiotic arm or placebo arm. A computer random number algorithm (1:1 allocation ratio) at Winclove probiotics B.V. will randomize women, using blocks of 4. A staff member at Winclove Probiotics B.V., who is not involved in the study, will sequentially label probiotic boxes (including number sachets with the probiotic or placebo product). The staff member will also create a sealed randomization list and sealed code break envelopes per participant in order to keep the trial investigators unaware of the allocation sequence and randomization code, and to maintain blinding until the end of the pilot trial. The randomization code will not be released until the last participant has finished the pilot trial. The CI, who is unaware of participant assignment in the allocation sequence, will distribute the sequentially numbered probiotic boxes. Participants will be assigned to a numbered box upon order of providing informed consent. Next to investigators, the participants, care providers and outcome assessor are blinded to the participant’s allocation. The Principal Investigator (PI) has access to the randomization data in case it is necessary to unblind. The blind may be broken for a serious and unexpected event, if it is essential for the medical management of subjects, or may provide critical safety information about the intervention that could have implications for the ongoing conduct of this trial. Sealed code break envelopes per participant are accessible within 24 h. In the event of a code break, the name of the code breaker, the signature and the date and time will be recorded on the outside of the envelope.

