### Measurements and outcomes

#### Primary outcome

The primary outcome will be assessed as follows: feasibility will be assessed in terms of (A) recruitment (quantitative and qualitative), (B) retention (quantitative) and acceptability will be assessed in terms of (C) compliance (quantitative) and (D) participants’ impressions and experiences during the pilot trial (quantitative).

The primary outcome of a full RCT would include effectiveness of the probiotic, compared to placebo, in reducing anxiety and depressive symptoms during pregnancy. For that reason, key outcome measures of this pilot study will inform whether or not to proceed with a full trial after this study, and if so, the revisions that should be made to the study protocol before conducting a full RCT. These outcomes include (B) retention rate, (C) compliance (i.e. proportion of participants taking ≥ 80% probiotic/placebo and proportion of participants filling in electronic questionnaires at all time points) and (D) participants’ experiences of participation and perspectives on joining this and future probiotic trials. Table 1 shows the outcomes, progression criteria (where applicable), key outcome measures and time points for each outcome of this pilot study.

**Table 1 Tab1:** Primary outcomes, (key) outcome measures, time points for each outcome and progression criteria for a full RCT

Primary quantitative outcomes	Outcome measure and time point for each outcome	Progression criteria for full RCT^a^
A) Recruitment	1) The proportion of contacted participants scoring above the threshold for anxiety or depressive symptoms and who accept the invitation to participate in the pilot trial throughout the study	30 participants recruited in 6 months
	2) The number of participants recruited at each site	No criteria set
B) Retention rate	2) The proportion of participants completing the study from enrolment (t0) to follow up (t4)*	≥ 90% of enrolled participants^b^
C) Compliance	3) The proportion of participants taking ≥ 80% probiotic/placebo product between t0 and t1*	90% of participants^c^
	4) The proportion of participants filling in electronic questionnaires at all time points (t0, t1 and t4)*	90% of participants
	5) The proportion of participants filling in the cry diary at t4	90% of participants
	6) The proportion of participants filling in evaluation form at t4	90% of participants

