#### Primary outcomes: quantitative

Recruitment: the CI will obtain data on the proportion of women agreeing to participate in the trial and the site of recruitment from the research database and Excel spreadsheet chart after completion of the pilot study and will report the data on Microsoft Excel spreadsheet charts (see “Study setting and recruitment”).Retention rate: dropouts and the reasons for withdrawal if known will be documented by the CI on case report forms (CRFs) throughout the pilot trial. New participants will not replace dropouts. Data on the proportion of women who complete the study will be collected from CRFs at the end of the study (see “Data management” and “Statistical analysis”).Compliance: the rates of adherence to probiotic/placebo intake, electronic questionnaires/evaluation form/cry diary and microbial, vaginal and hair samples will be recorded by the CI on CRFs and Microsoft Excel spreadsheet charts throughout the study (see also “Strategies to improve adherence to intervention protocol for information”).Participants’ impressions and experiences: participants will be requested by the CI to fill in a self-created evaluation form within 1 week after completion of the pilot trial at home. The questionnaire includes nine questions: five questions on how the woman experienced (1) filling in questionnaires during the pilot trial (i.e. length, number of questionnaires, electronic method), (2) collecting their own and infant stool samples and vaginal samples (i.e. number of samples, explanation about method of collection, potential difficulties in collecting samples) and (3) having hair samples collected. Four items measure level of satisfaction: two open-ended questions stating “Regarding the study in general, which aspects did you experience as most positive and negative?” and “Do you have any general remarks regarding execution and organization of this study?”. For the other two questions, participants rate the perceived burden of the trial on a scale of 0–10 (0 “no burden”, 10 “very large burden”) and likelihood of participating in a similar trial in the future (0 “no chance of future participation”, 10 “very high chance of future participation”).

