#### Primary qualitative outcomes

Qualitative content analysis following principles of the framework approach will be undertaken for outcome (A) recruitment [73, 74]. To develop an analytical framework, two researchers will read through all answers from Microsoft Excel spreadsheet charts and will apply inductive “open coding” (i.e. label what they consider to be relevant from as many perspectives as possible). After coding the first transcripts, the labels applied will be compared between the two researchers to agree on a set of codes and these codes will be grouped to form themes and categories. The analytical framework, including the codes and themes, will consequently be used to index all transcripts. Data will be summarized by category and put into a Microsoft Excel spreadsheet chart to generate a matrix. The chart consists of participants (rows) and emergent qualitative themes (columns) and will be used to identify similarities and differences between participants’ expressed thoughts. The qualitative findings will be described in detail, supported by quotes from participants.

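### Theme prevalence in primary outcome D (1–3) is a share of codes, not a share of women, so its size does not show how widespread a view is

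*Protocol article*

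**What the plan says.** The Objectives section lists, as the fourth primary objective, "participants’ impressions and experiences during the pilot trial (quantitative"). Under Measurements and outcomes, Primary outcome, the key outcome measures that inform whether to proceed to a full trial and what to revise include participants' "experiences of participation and perspectives on joining this and future probiotic trials".

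Under Statistical analysis, Primary quantitative outcomes, items D (1–3) are to be handled by content analysis: "the main themes and categories of participants’ responses will be identified" and then quantified. The rule for quantifying them is: "The prevalence of coded themes will be calculated as a percentage of the total number of identified coded themes". An earlier sentence in the same paragraph says, for all primary outcomes, that numbers and percentages will be given for categorical variables.

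The data come from the evaluation form described under Primary outcomes: quantitative. One of its open questions reads: "Regarding the study in general, which aspects did you experience as most positive and negative". The coding method, to which D (1–3) is cross-referred, is set out under Primary qualitative outcomes. The coders are to "label what they consider to be relevant from as many perspectives as possible", and "The chart consists of participants (rows) and emergent qualitative themes (columns"). That section describes the method for the recruitment outcome.

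Table 1 sets no progression criterion for D1, D2 or D3. The criteria for D are the two 0–10 ratings, D4 (perceived burden) and D5 (future participation).

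**The concern.** Prevalence normally means a proportion of people, and the retention and compliance proportions in Table 1 are proportions of participants. For D (1–3) the denominator changes to codes while the word prevalence is kept. A reader will tend to take such a percentage as the share of women who hold the view.

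The planned figure also depends on something unrelated to the theme itself, namely how much else the respondents wrote. The same number of women raising the same difficulty gives a smaller percentage when the group raises more other themes, and a larger one when many women leave the question blank. Women who write more contribute more to the denominator.

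What is at stake is interpretation. D (1–3) are the D items that point to particular procedures (questionnaires, sample collection, organization), whereas D4 and D5 are global ratings. Someone deciding what to adjust before the full trial will want to know how many women found a procedure difficult, and the planned percentage does not say.

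**Working it through.** The plan states no numerical value on this point, so there is no figure to reproduce. The check compares the planned measure with the share of women.

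**Inputs**
- Denominator of the planned measure: total identified coded themes (Primary quantitative outcomes).
- Number of women, n: at most 40 ("The 40 women will be randomly allocated to either the probiotic arm or placebo arm"), fewer if evaluation forms are not returned.
- Several themes per woman are possible: the open question asks for aspects in the plural, both positive and negative, and the coding rule invites several labels per answer.
- Mean number of themes per respondent, k: **not in the document**. It is an assumption, shown from 0.5 to 4.

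**Formulas**
- Let h be the number of women who raise a given theme, each counted once for that theme.
- Total codes: T = n × k.
- Planned measure: h / T = h / (n × k) = (h / n) / k.
- Share of women: h / n.
- Ratio of planned measure to share of women: 1 / k. The two agree only at k = 1.

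**Results with n = 40**

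| Women raising the theme | Share of women | k = 1 | k = 2 | k = 3 | k = 4 |
|---|---|---|---|---|---|
| 20 | 50% | 20/40 = 50.0% | 20/80 = 25.0% | 20/120 = 16.7% | 20/160 = 12.5% |
| 30 | 75% | 30/40 = 75.0% | 30/80 = 37.5% | 30/120 = 25.0% | 30/160 = 18.8% |
| 36 | 90% | 36/40 = 90.0% | 36/80 = 45.0% | 36/120 = 30.0% | 36/160 = 22.5% |

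**Opposite direction.** With many blank answers, say k = 0.5, T = 20. A theme raised by 10 women (10/40 = 25%) is then reported as 10/20 = 50%.

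**Incomplete return.** With 36 forms, a theme raised by 18 women (50%) gives 18/36 = 50% at k = 1, 18/72 = 25% at k = 2 and 18/144 = 12.5% at k = 4. The ratio is again 1/k.

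**Order of themes.** Within one question all themes share the same T. If each woman counts once per theme, a theme raised by 20 women always stands above one raised by 10. Only the level of the percentages changes.

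**Meaning of the denominator.** The phrase could mean coded mentions or distinct themes. The arithmetic uses mentions, because a count of women over a count of distinct themes would not be a bounded percentage. On neither reading is the denominator women.

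**The case against.** The strongest reply is that the sentence hides nothing. It speaks of the prevalence of themes, gives its denominator in the same line, and a share of codes is a recognisable summary in content analysis. That stands in part: the measure is legitimate under its own name. What remains is that it is called prevalence and that no woman-level figure accompanies it.

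A second reply is that the general line on numbers and percentages, together with the participant-by-theme chart, already allows women to be counted. The chart does make the count easy. But the sentence on themes is the specific rule, it fixes a different denominator, and it is not overridden by the general line. For the same reason this is not a detail left to a fuller document.

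A third reply is that the harm is small. This stands. No sample size, error rate or treatment comparison depends on these figures. Procedures that women failed to complete would show in the compliance outcomes of Table 1, which are proportions of participants with 90% criteria, although those would miss difficulties among women who complied.

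Three stronger readings are tempting, and the document does not support them:
- A reader might infer that theme percentages decide which procedures are revised. Table 1 sets no criterion for D1 to D3 and does not mark them as key; participants' experiences inform the decision, without a rule based on theme percentages.
- A reader might infer that a widespread complaint would rank as a minor theme. Within a question the order is kept when each woman counts once per theme.
- A reader might infer that the measure always understates. It does so only when k exceeds 1.

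**Conclusion.** The point holds as a matter of what the reported percentage means. The planned measure is the share of women divided by the mean number of themes per woman. The wording of the form and the coding rule make more than one theme per woman likely, in which case the percentages will be too low as statements about women: by half at k = 2 and to a quarter at k = 4. Those sizes are illustrations, since the document gives no k, and they assume that each woman counts once per theme. With k below 1 the error reverses.

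The consequence is limited to the size of the percentages and to how widespread a difficulty appears. Percentages from questions with different k would also not be on the same scale, but the protocol plans no comparison across questions, so nothing more should be read into that. This is a free improvement, not a flaw that endangers the pilot's conclusions.

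**What to change.** Replace the sentence on theme prevalence under Primary quantitative outcomes. For each D (1–3) theme, report the number and percentage of women returning the evaluation form who mention it at least once, each woman counted once per theme, and state the number of forms returned. The share of codes may be kept as a supplement if it is labelled as such. A confidence interval is optional for an outcome that is declared descriptive.

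No new data or analysis are needed. Laying out the evaluation-form responses in the same participant-by-theme chart gives the count directly, so the only change is the denominator and a line of text.
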